### Data Collection and Measurement Tools

#### Presimulation Questionnaire

This questionnaire will include demographic data (gender, age, year of graduation, number of previous experiences with simulation, learning style, and curriculum followed), degree of self-assessed subjective stress, and self-evaluation of clinical reasoning performances (both using a 10 point Likert-type scale question).

#### In-Simulation Clinical Reasoning Assessment

In constructing the simulation scenario and vignette, defined cues will be embedded to stimulate hypothesis generation using System-1 of clinical reasoning. After reading the initial patient presentation in the vignette, residents are asked to submit their diagnostic hypothesis by writing. Then, during the scenario, the participant’s verbalization (which is also stimulated by given cues from the nurse) of diagnosis coming to mind will be audio recorded. Both the written and audio-recorded hypotheses will be compared to the diagnoses generated by an expert panel that will be submitted to the same scenario. For example, the presence of thrombocytopenia during the data confirmation part should lead to verbalization of (1) bacterial infection, (2) viral infection, (3) intrauterine grown retardation, and (4) platelets immunization. The presence of skin lesions during the data confirmation part should lead to verbalization of (1) herpetic infection, (2) bacterial infection, and (3) varicella infection.

Iterative discussions supported by the Clinical Reasoning Assessment Tool during SID have been designed to allow development and exploration of System-2 of clinical reasoning regarding data collection, diagnostic hypotheses generation, new data interpretation, and management plan. In the classical approach, it is hypothesized that System-2 is discussed during the debriefing period after the simulation. Exploration of how both simulation approaches impact on performance of System-2 will be done during the semistructured interviews (see below).

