We believe that changes in the organization of a simulation session could allow better assessment of both System-1 and 2 of the reasoning process. First, *reflection-in-action* should be encouraged by concurrent verbalization to let the tutors know about the student’s intuitive System-1 thinking during management of a patient [11-13]. Second, *reflection-on-action,* which reflects analytical System-2 should be encouraged by in-simulation interruptions at key moments of the clinical reasoning process [48,49]. These interruptions could be assimilated to a dynamic and decision-dense environment where clinical reasoning constructs must be considered, as studies suggest that the average time on particular tasks is limited to less than 2 minutes, and interruptions occur every 2 to 10 minutes in the emergency department [50-52]. Finally, the active experimentation of newly acquired conceptualizations in a subsequent part of the scenario may avoid the learner’s return to actions based on habits and nonreflective experience [32]. Based on these arguments, we present a new approach of SBE, called simulation with iterative discussions (SID). The simulation session is designed as a single scenario with a computerized mannequin where the instructor interrupts the flow of the scenario at three key moments to cue residents towards the appropriate medical management of the case. The objectives of the session are to build a scaffold of clinical reasoning competencies throughout the scenario while continuing to manage the patient, and to improve concept acquisition and retention with spaced learning. We believe that a closer assessment of both System-1 (by concurrent verbalization during patient management) and System-2 (during iterative discussions) will improve students’ capability to self-improve clinical reasoning skills in an authentic setting.

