#### Description of the Intervention

The SID approach (Figure 2a) consists of a scenario interrupted at three moments and followed by a short debriefing. According to Kuhn’s steps of the medical reasoning process [60], the session is divided into “data gathering”, “data integration,” and “data confirmation”. Each part consists of two phases. First, the participant is asked to manage a simulated patient based on a real-life and complex case. Complexity, uncertainty and environmental factors such as doctor, patients, and encounter factors [25] are voluntarily embedded. The participant is also asked to verbalize his or her first *intuitive* diagnosis as it comes in mind by System-1 activation. Second, the scenario stops and the instructor questions the participant on his clinical reasoning process at that point in time by System-2 activation. Each interruption must be as short as possible in order to keep the trainee in action, and is ended by a one-sentence reconceptualization of the scenario by the instructor before pursuing the scenario (for the two first stops). Discussions include questions regarding data gathering and the rationale of ordered investigations (first stop), data integration, and how investigation results helped reach a diagnosis (second stop), and finally data confirmation and how the management decisions were reached (third stop). There is neither feedback nor guidance from the instructor during the stops in order to not interfere with the participant’s ongoing clinical reasoning process. These stops are “discussions” and not “debriefings”. A short general debriefing ends the session, and provides feedback on reasoning, procedural skills, and knowledge by highlighting the learnt key messages.

The classical approach (Figure 2b) consists of a scenario with no intervention provided by the instructor until debriefing. As in the SID approach, the participant must verbalize his reasoning process and the diagnostic hypotheses as they come to mind during the scenario. Immediately after the scenario, a facilitated debriefing is performed. This debriefing lasts two to three times the length of the scenario and focuses on the participant’s clinical reasoning skills.

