#### Scenario

In order to stimulate the reasoning process, the chosen topic has to be realistic, and hold a range of differential diagnoses. Investigations should be necessary to precise or refute diagnoses in the absence of specific clinical signs. Uncertainty needs to be deliberately embedded. Management must be complex with controversies concerning treatments. Moreover, a range of environmental factors and events can be added to challenge team members by generating dissonance and failures in order to optimize efficiency of simulated team training and adult learning. The amount of provided information has to be minimal and nonspecific aiming to stimulate additional questions from the participant. Answers to participants’ questions must be standardized and should cover a range of possible differential diagnoses. Finally, procedural and relational skills must be embedded in order to portray as closely as possible the real-life environment.

The general structure of the scenario must follow three parts so it can be performed in a single run-through (for the classical approach) or interrupted (for the SID approach). First, a nonmonitored patient presents with minor symptoms but remains clinically stable. The participant has to check the vital signs, ask the nurse for the history and the results of the physical examination, and order investigations. Second, the patient presents with acute collapse. The participant has to interpret investigation results while managing the acutely ill patient. Third, the participant must present a summary of the situation and a treatment plan to his supervisor while pursuing management of the patient. For the SID approach, the scenario is stopped at two times: (1) after ordering investigations, and (2) after receiving results of the investigations and prior to the call from the supervisor. The last stop occurs at the end of the scenario.

Based on these principles, the chosen scenario consists of an infant with disseminated herpes simplex virus infection presenting with secondary septic shock. A newborn will present with tachycardia and will evolve towards hypoxemia and hypotension, requiring intubation and volume expansion. Laboratory findings will reveal viral sepsis with leucopenia, thrombocytopenia, increased C reactive protein, and elevated liver enzymes. Finally, skin blisters will appear during the transfer of information from the participant to the supervisor and will confirm the diagnosis.

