### Data Analysis

This is an exploratory study that will aid in planning a future larger randomized controlled trial. The target population of residents enrolled in the General Pediatrics and Neonatal-Perinatal Medicine programs represents approximately 50 residents. Based on literature from qualitative research inquiry, the adequate sample size consists of the number of participants at which saturation of data is achieved. This well-described process permits cessation of recruitment when additional data does not bring new properties to unsaturated categories [67]. Different authors agree that saturation is reached after 20 to 25 participants [67,68].

Quantitative data will be analyzed using SPSS 20.0 (IBM SPSS, Chicago, IL). Data will be analyzed using descriptive statistics for all variables. For each Likert-scale type question, a significant cut-off will be pre-established. Comparison of positive versus negative responses will be done with the use of chi-square and Fischer’s exact test for nonparametric variables. Number, nature, and order of diagnostic hypotheses will be compared to the responses of a panel of 10 neonatologists from our hospital. A multivariate analysis will be used to investigate potential effects of graduation year, gender, and prior simulation experience on the residents’ evaluation of their clinical reasoning. Statistical significance will be defined as a probability value of <.05.

Qualitative data will help describe if SID allows better assessment of System-1 and 2 of clinical reasoning compared to the classical approach of simulation. Data from audio-recorded semistructured interviews will be analyzed using NVivo 9.0 software. Analysis will occur as data collection pursues. Recurring themes or distinctive aspects about each student’s response will be noted. These notes will be reviewed and expanded as the research continues until saturation of data. Data will be de-identified so that all participants will remain anonymous. Through content analysis, the information will then be categorized according to the principle of convergence [69]. The research team will use deductive analysis and review of all written transcripts.

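### The diagnostic hypotheses, the only quantitative outcome that is not self-report, have an expert panel rather than the other arm as stated comparator, are not split at the point where the arms diverge, and include a cue placed in the wrong scenario part

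*Protocol article*

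**What the plan says.** The aim (Protocol article, Aim of the Study and Working Hypotheses) is a comparison of SID with the classical approach.

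**Collection of hypotheses** (In-Simulation Clinical Reasoning Assessment). "After reading the initial patient presentation in the vignette, residents are asked to submit their diagnostic hypothesis by writing". Spoken diagnoses are then recorded during the scenario in both arms. The comparison is described once there: "Both the written and audio-recorded hypotheses will be compared to the diagnoses generated by an expert panel". Data Analysis repeats it: "Number, nature, and order of diagnostic hypotheses will be compared to the responses of a panel of 10 neonatologists from our hospital".

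**Where the arms differ.** Under Scenario, the two SID stops within the scenario come at "1) after ordering investigations, and (2) after receiving results of the investigations and prior to the call from the supervisor". Under Description of the Intervention, each of these stops "is ended by a one-sentence reconceptualization of the scenario by the instructor before pursuing the scenario". The classical arm has no instructor intervention until its debriefing.

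**What the stops are for.** The Introduction says the instructor "interrupts the flow of the scenario at three key moments to cue residents towards the appropriate medical management of the case". Description of the Intervention says that the stops contain no feedback and no guidance.

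**Example cue.** The measurement section says that "the presence of thrombocytopenia during the data confirmation part should lead to verbalization of" four named diagnoses.

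**The concern.** A randomised comparison needs an outcome contrasted between the randomised groups. For the hypotheses, the only contrast on paper is residents against specialists. That shows how far residents are from experts, not whether SID differs from classical simulation. If each arm were tested against the panel and the two results read side by side, an apparent arm difference could arise where none exists.

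Timing is the second issue. The written response and the speech before the first stop precede any scheduled difference in instructor handling, so they cannot carry an effect of the stops. Unless they are kept apart from later hypotheses, they dilute any arm contrast.

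Third, spoken hypotheses are meant to show intuitive System-1 reasoning and the stops analytical System-2 reasoning. If a cue is scored after SID residents have been questioned about it, the System-1 score in that arm contains System-2 work, and the working hypotheses that separate the two systems cannot be read from it. The study is meant to help plan a larger trial, so an outcome that cannot be interpreted would carry forward.

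**Working it through.** **1. Which outcomes are quantitative and not self-report?** The pre- and postsimulation questionnaires are self-rated Likert-type items. The interviews are qualitative. The Clinical Reasoning Assessment Tool is an aid for the instructor. Only the diagnostic hypotheses remain.

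**2. Which comparisons does Data Analysis name?**
- Chi-square and Fisher tests: positive against negative questionnaire responses.
- Multivariate analysis: effects of graduation year, gender and prior simulation experience on self-evaluation; arm is not listed.
- Hypotheses: against the panel of 10.

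No sentence contrasts the hypotheses between SID and classical.

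**3. Timeline, combining Scenario and Description of the Intervention.**

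| Point | SID | Classical | Hypotheses |
|---|---|---|---|
| Vignette | read | read | written |
| Part 1: investigations ordered | manages, verbalizes | manages, verbalizes | spoken |
| Stop 1 | questions on data gathering, then reconceptualization | nothing | – |
| Part 2: collapse, results interpreted | manages, verbalizes | manages, verbalizes | spoken; thrombocytopenia becomes known |
| Stop 2 | questions on how the results led to a diagnosis, then reconceptualization | nothing | – |
| Part 3: summary to supervisor, skin lesions | manages, verbalizes | manages, verbalizes | spoken; article places both example cues here |
| End | third stop, short debriefing | full debriefing | – |

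The first two rows of hypotheses precede the first scheduled difference. The skin lesions belong in part 3. Thrombocytopenia is a laboratory result, known in part 2 and discussed at stop 2 in SID only, so its assignment to data confirmation conflicts with the scenario. All classical hypotheses are recorded before that arm's debriefing, where its teaching takes place.

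**4. Size.** The article gives no effect size, standard deviation or power, so there is no figure to reproduce. What follows rests on assumptions.

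*Panel comparison in place of an arm contrast.* Simulation, 20,000 runs: two identical arms of 10 to 25 residents, normal scores with SD 1, both 0.5 to 1.0 SD below one panel of 10, each t-tested against the panel at two-sided 0.05. One arm was significant and the other not in 20% to 33% of runs. A direct test between the arms was significant in about 5%.

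*Not separating the parts.* Assume a standardised difference d = 0.8 confined to hypotheses after stop 1, a share f of a combined score coming from before it, and an unchanged SD. With n per arm, power ≈ Φ(d(1 − f)√(n/2) − 1.96). The figure n = 25 assumes that all of the approximately 50 residents enrol and split equally; n = 10 to 12 corresponds to the 20 to 25 participants cited for saturation.
- n = 25, f = 0: Φ(0.8 × 3.536 − 1.96) = Φ(0.87) = 81%.
- n = 25, f = 0.25: Φ(0.16) = 56%.
- n = 25, f = 0.5: Φ(−0.55) = 29%.
- n = 25, f = 0.75: Φ(−1.25) = 11%.
- n = 10 to 12: 43% to 50% at f = 0, and 14% to 16% at f = 0.5.

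*Letting the SD change with the sum.* Take four windows (written, parts 1 to 3) of unit variance, correlation ρ = 0.3, and an effect in the last two only. In units of the per-window effect:
- All four summed: 2/√(4 + 12 × 0.3) = 0.725.
- Parts 2 and 3 only: 2/√(2 + 2 × 0.3) = 1.240.
- Parts 2 and 3 adjusted for the written score: squared correlation (2 × 0.3)²/2.6 = 0.138, so 1.240/√(1 − 0.138) = 1.336.

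The information ratio of the sum to the adjusted analysis is (0.725/1.336)² = 0.29. The same steps give (0.877/1.361)² = 0.42 at ρ = 0.1 and (0.632/1.414)² = 0.20 at ρ = 0.5.

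**The case against.** The best defence is that the panel is a scoring key. The lists of expected diagnoses per cue look like one, and concordance with a key can then be compared by arm. This is a condensed article, and a fuller document may name that contrast. A reader might infer that no arm comparison will be made; the text does not exclude one. What stands is that both descriptions of the analysis name the panel and neither names the arms.

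A reader might also infer that written and spoken hypotheses are pooled into one score. The article does not say so. Order is listed as an attribute, and the examples are given cue by cue, which leaves room for staged scoring. It is accurate only to say that the parts are not separated, and the dilution figures describe a score that the article never defines.

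A third tempting reading is that instructor input biases the result and always towards SID. The stops are part of what SID residents are randomised to, so their effect is not bias in itself. An interruption or restatement could also distract or anchor a resident. Several places in the article rule out feedback or guidance at the stops, against one Introduction sentence about cueing. That conflict still needs resolving, because it decides whether later SID hypotheses reflect the resident's reasoning or the instructor's wording.

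The thrombocytopenia label may be a copying slip, since both examples share a phrase and are introduced as illustrations. It still describes how hypotheses would be scored, and scoring it as written changes what is counted.

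Finally, the study is exploratory, looks to interviews for System-2 effects, and admits that it lacks a robust pre and post assessment. This limits how much rests on the hypotheses; it does not supply the missing contrast.

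**Conclusion.** The concern holds in a limited form. For the one quantitative outcome that is not self-report, the article states a comparator that does not answer its aim and does not separate hypotheses from before and after the arms diverge. It assigns one example cue to a part that its own scenario contradicts, and makes two statements about the stops that cannot both stand. These points rest on the text alone.

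The size is not known. The discordance of 20% to 33% applies only if arms are judged separately against the panel. The fall in power from 81% to 29%, and the information ratio of 0.29 (0.42 to 0.20), apply only if a summed score is used, under the assumptions shown. Any effect of instructor wording probably favours SID, but its direction is not certain.

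Even after correction, later differences show performance under SID within the scenario. They cannot show what the classical approach teaches, because that arm is measured before its debriefing.

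**What to change.** Before scoring begins:

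- State that the panel's responses are the scoring key. Score each resident's concordance by scenario part: written, before stop 1, between stops 1 and 2, after stop 2, using the matched scenario points in the classical arm.
- Name the contrast: SID against classical on hypotheses voiced after stop 1, adjusted for the written vignette score and the novice/expert stratum.
- Report speech before stop 1 separately and do not adjust for it. It follows allocation in a nonblinded study, and the verbalization request is worded differently by arm: a first intuitive diagnosis in SID, the reasoning process and hypotheses in classical.
- Move the thrombocytopenia cue to data integration and count only verbalizations before stop 2. Leave the skin lesions in data confirmation.
- Reconcile the Introduction's statement about cueing with the Methods' statement that there is no feedback or guidance. Standardise the reconceptualization sentence so that it restates only facts already disclosed.
- State the limit on interpretation given in the verdict.

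The recordings and the written response are already planned. The cost is slightly more scoring work by part, plus edits to the scoring sheet, the analysis wording and two scripted sentences.

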#### Postsimulation Questionnaire

Postsimulation questionnaire (Multimedia Appendix 1) will assess residents’ self-reported improvement in clinical reasoning and level of satisfaction regarding the simulation approach (both using a 10 point Likert-type scale question). The questionnaire will be designed based on previous literature [63-65] and will be pilot tested with three residents. According to the simulation approach, residents will also complete 5 to 12 questions asking them to rate statements using a four-point Likert-type scale, ranging from 1 (strongly disagree) to 4 (strongly agree).

#### Semistructured Interviews

An individual semistructured interview will explore “how” and “why” students’ clinical reasoning ability develops through both simulation approaches (SID or classical). Interviews will be conducted using techniques inspired from the explicitation interview during which the interviewer supports the participant, without induction, toward the evocation of a specified experience [66]. After icebreakers, interviews will be constituted of two distinctive parts. First, the interviewer will explore the residents’ reasoning process during the simulation experience. Second, he will focus on residents’ perception of the simulation experience, including possible advantages and challenges of each simulation type, possible improvements to each methodology, and the perceived impact of SID on the participants’ learning. Interviews will be audio recorded and then transcribed for analysis.

### Data Analysis

This is an exploratory study that will aid in planning a future larger randomized controlled trial. The target population of residents enrolled in the General Pediatrics and Neonatal-Perinatal Medicine programs represents approximately 50 residents. Based on literature from qualitative research inquiry, the adequate sample size consists of the number of participants at which saturation of data is achieved. This well-described process permits cessation of recruitment when additional data does not bring new properties to unsaturated categories [67]. Different authors agree that saturation is reached after 20 to 25 participants [67,68].

Quantitative data will be analyzed using SPSS 20.0 (IBM SPSS, Chicago, IL). Data will be analyzed using descriptive statistics for all variables. For each Likert-scale type question, a significant cut-off will be pre-established. Comparison of positive versus negative responses will be done with the use of chi-square and Fischer’s exact test for nonparametric variables. Number, nature, and order of diagnostic hypotheses will be compared to the responses of a panel of 10 neonatologists from our hospital. A multivariate analysis will be used to investigate potential effects of graduation year, gender, and prior simulation experience on the residents’ evaluation of their clinical reasoning. Statistical significance will be defined as a probability value of <.05.

Qualitative data will help describe if SID allows better assessment of System-1 and 2 of clinical reasoning compared to the classical approach of simulation. Data from audio-recorded semistructured interviews will be analyzed using NVivo 9.0 software. Analysis will occur as data collection pursues. Recurring themes or distinctive aspects about each student’s response will be noted. These notes will be reviewed and expanded as the research continues until saturation of data. Data will be de-identified so that all participants will remain anonymous. Through content analysis, the information will then be categorized according to the principle of convergence [69]. The research team will use deductive analysis and review of all written transcripts.

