### Study Design

This is a prospective exploratory nonblinded randomized mixed-methods study. Both quantitative and qualitative research methods will be used simultaneously as to comprehensively explore how clinical reasoning develops through both simulation modalities.

Randomization will be stratified according to two different groups depending on their level of exposure to the NICU: (1) novice residents (PGY1 and 2, exposed to less than 8 weeks to the NICU), and (2) expert residents (PGY3-6, exposed to at least 8 weeks to the NICU). These residents have been respectively exposed to at least 5 or 15 simulation sessions during their residency training. Residents will be randomly (by draw of names) allocated by the primary investigator to group A or group B (Figure 1). Group A will be exposed to the SID approach, whereas group B will be exposed to the classical approach of simulation. Participants will be scheduled to complete the study protocol in 60 minutes. In the first 5 minutes, participants will complete the presimulation questionnaire and receive a brief introduction including a period to get physically familiarized with the mannequin (SimNewB; Stavanger, Norway). In the next 30 minutes, residents will complete the clinical simulation scenario after reading a clinical vignette. At the end of the session, participants will have 5 minutes to complete the postsimulation questionnaire (see Multimedia Appendix 1). The course will end with a 20 minutes semistructured interview.

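### Cutting the 10-point ratings into positive and negative gives up power that a full-scale comparison using arm and stratum would keep

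*Protocol article*

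**What the plan says.** All references are to the protocol article.

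- **Cut-off and test (Data Analysis).** "For each Likert-scale type question, a significant cut-off will be pre-established". The next sentence reads "Comparison of positive versus negative responses will be done with the use of chi-square and" Fisher's exact test. The groups being compared are not named. The threshold is "Statistical significance will be defined as a probability value of <.05".
- **Outcomes (Postsimulation Questionnaire).** Self-reported improvement in clinical reasoning and satisfaction are each rated on a 10-point scale. Further statements are rated on a four-point scale.
- **Baseline (Presimulation Questionnaire).** Each resident gives a "self-evaluation of clinical reasoning performances (both using a 10 point Likert-type scale question"). No stated inferential analysis uses it.
- **Randomisation (Study Design).** "Randomization will be stratified according to two different groups depending on their level of exposure to the NICU": novices are PGY1-2 and experts PGY3-6.
- **The one model (Data Analysis).** "A multivariate analysis will be used to investigate potential effects of graduation year, gender, and prior simulation experience on" residents' ratings of their own reasoning. Arm is not among the listed factors.
- **Numbers (Data Analysis).** The target population "represents approximately 50 residents". The sample size rationale is qualitative: "Different authors agree that saturation is reached after 20 to 25 participants". No power calculation is given.

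**The concern.** The 10-point ratings are the quantitative evidence for the second working hypothesis (greater self-progression with SID) and for the satisfaction result expected in the Discussion. Splitting a 10-point rating in two treats a 7 and a 10 as identical, and a 6 and a 7 as opposites, if the cut falls between 6 and 7. The resulting 2×2 test also ignores the factor on which randomisation was stratified and the baseline rating already in hand.

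The study can enrol about 50 residents at most, and may stop at 20 to 25 if saturation governs recruitment. At that size, lost information matters. A real difference between the two formats would more often be reported as not significant, and the study is meant to help plan a larger randomised trial.

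**Working it through.** The article states no power, effect size, SD or cut-off, so there is no figure of its own to reproduce. The check compares the stated tests with a full-scale test on the same assumed data.

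**Inputs from the article**
- Significance level 0.05. Two-sided is assumed, as sidedness is not stated.
- About 50 residents, so 50/2 = 25 per arm if all take part and the split is equal.
- Saturation at 20 to 25 participants, so about 10 to 12 per arm.

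**Assumptions**
- The underlying rating is normal with equal SD in both arms and a true effect d = 0.8 SD (0.5 and 1.0 as sensitivity).
- *Central cut*, midway between the arm means: proportions positive are Φ(−0.4) = 0.34 and Φ(0.4) = 0.66.
- *Off-centre cut*, passed by 80% of the classical arm: 0.80 against 0.95.

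**Methods**
- *Full scale:* t-test power from the noncentral t with noncentrality d·√(n/2) and 2n − 2 degrees of freedom. For d = 0.8 the noncentrality is 0.8·√12.5 = 2.83 at 25 per arm and 0.8·√6 = 1.96 at 12 per arm.
- *Cut score:* exact enumeration of all pairs of binomial counts, adding the probability of those with p < 0.05, for Fisher and for chi-square without continuity correction.
- *Share of power lost:* 1 − (power on cut score)/(power of t-test).

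**Results, d = 0.8**

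| Per arm | Cut | Fisher | Chi-square | t-test | Lost, chi-square | Lost, Fisher |
|---|---|---|---|---|---|---|
| 25 | central | 53.8% | 65.2% | 79.1% | 18% | 32% |
| 12 | central | 22.8% | 37.9% | 46.6% | 19% | 51% |
| 25 | off-centre | 19.7% | 38.0% | 79.1% | 52% | 75% |
| 12 | off-centre | 4.0% | 11.8% | 46.6% | 75% | 91% |

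For example, 1 − 65.2/79.1 = 0.18 and 1 − 22.8/46.6 = 0.51. With the off-centre cut, the average expected negative count per arm is 0.125 × 25 = 3.1 or 0.125 × 12 = 1.5. These are small cells, where Fisher is the usual choice.

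**Sensitivity to effect size (central cut, 25 per arm)**
- d = 0.5: Fisher 23.1%, chi-square 32.9%, t-test 41.0%. The loss is 20% (chi-square) to 44% (Fisher).
- d = 1.0: Fisher 74.1%, chi-square 82.7%, t-test 93.4%. The loss is 11% to 21%.

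**Sample size for 80% power (d = 0.8, central cut)**
- Full scale: 2(1.96 + 0.84)²/0.8² = 24.5, so 25 per arm.
- Cut score: (1.96·√(2·0.5·0.5) + 0.84·√(2·0.345·0.655))²/0.311² = 39.4, so 40 per arm, or 46 with continuity correction.
- The whole population therefore just suffices on the full scale and falls short on the cut score.

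**Does this depend on normality?** Scores simulated as round(6.5 + 1.5z), limited to 1-10, with 2,000 runs per setting, gave:
- 12 per arm: Mann-Whitney 42%, Fisher at a cut of 7 or more 20%.
- 25 per arm: Mann-Whitney 75-76%, Fisher 46-47%.

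The gap remains with a rank test on a bounded 10-point scale.

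**Baseline rating.** A covariate correlated r with the outcome multiplies the residual SD by √(1 − r²), which is 0.95 at r = 0.3 and 0.87 at r = 0.5. The article gives no basis for r. The pre-session item rates performance and the post-session item rates improvement, so r could be near zero. No gain from the baseline is counted in the table.

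**The case against.** The strongest case on the other side has several parts.

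- **Exploratory study.** It makes no power claim, and the Discussion discloses both the small sample and the lack of a robust pre/post assessment. An unadjusted chi-square or Fisher test with a cut-off fixed in advance does not bias the comparison of randomised arms. This stands and limits the point to efficiency. It does not make the cut a good choice, because a small sample makes discarded information more costly.
- **Size of the loss.** A reader might infer that most of the available power is lost. That holds only for Fisher at about 12 per arm (51%) or for an off-centre cut. With a central cut at 25 per arm the loss is 18% to 32%.
- **Large gains from baseline adjustment.** These would need the performance rating to be repeated after the session. The article describes an improvement rating instead, so no such gain can be claimed.
- **Means and SDs.** A reader might infer that the plan cannot supply them for the larger trial. The Data Analysis section promises descriptive summaries of every variable, which can include them by arm. What is not stated is an interval for the arm difference.
- **The multivariate model.** It reads as an analysis of predictors, so leaving out arm is not an error in itself, and an article may abbreviate the covariate list. Graduation year may also carry much of the novice/expert split. The claim that its covariates are collinear with the stratum is not supported: Study Design gives only minimum numbers of earlier sessions, while each resident's own number is recorded.
- **Groups compared.** The text does not say that positive and negative responses are compared between arms. The hypotheses make that the natural reading. If it is wrong, no test of these ratings between arms is stated at all.

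**Conclusion.** The point holds as a recommendation on efficiency. The article states a method rather than leaving one open, and that method gives up information on its main quantitative outcomes. At an assumed 0.8 SD effect and a central cut, the loss relative to the t-test is about a fifth to a third of its power at 25 per arm and about a fifth to a half at 12 per arm. It is greater with an off-centre cut. These sizes rest on an assumed effect, cut-off and distribution, since the article gives none of them; the direction of the loss is the same in every setting tried.

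The documents do not support reading this as an invalid or biased analysis, or as one that loses most of its power in general.

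**What to change.** 1. Analyse the 10-point improvement and satisfaction ratings on their full scale with a linear model on arm and novice/expert stratum.
2. For the clinical-reasoning rating, add the pre-session self-rating as a covariate. State that the gain depends on an unknown correlation, because the post-session item rates improvement.
3. Report the SID-minus-classical mean difference with its 95% CI and the SD.
4. Add a rank-based check stratified by novice/expert (van Elteren test).
5. Keep percent positive at the pre-set cut-offs as description.
6. If the multivariate model is meant to inform the arm comparison, include arm in it.

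The cost is a change of analysis wording; all the variables are already collected. The drawback is that 10-point scores are treated as approximately continuous, which the rank-based check covers.
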